### Masking

GPs will be masked because they are not informed which group the patient is allocated to. Tai Chi Chuan teachers and the participants cannot be masked. Both research assistants who perform the measurements and the researcher who performs the data analyses will be masked.

### Control group

Participants in the control group receive 'usual care' without an additional intervention. 'Usual care' means that they, as before, can use or apply for all available services in the area. Participants in both the control and the intervention group will receive a brochure containing general information on how to prevent falls in and around the house.

### Intervention group

Participants in the intervention group will receive in addition to the 'usual care' Tai Chi Chuan lessons.

The Tai Chi Chuan form is based on the one used by Wolf et al. [11]. This form turned out to be appropriate for the elderly because all components of movement that typically become limited with aging are emphasized. The ten positions are easily comprehensible. It is derived from the Yang style and consists of a form with ten positions: 1. Opening; 2. Grasping the Sparrow's Tail, Left; 3. Grasping the Sparrow's Tail, Right; 4. Cloud Hands; 5. Repulse Monkey; 6. Part Wild Horse's Mane; 7. Brush Knee Twist Step; 8. Lift Kick Left; 9. Lift Kick Right; 10. Closing. The ten positions are linked together in a continuous, smooth-flowing form.

Four Tai Chi Chuan-teachers are available to give the lessons. All are qualified to give the lessons and are experienced in working with elderly. Together they will develop and finalize the Tai Chi Chuan-protocol.

In the literature [8] the recommended frequency of lessons varies from once a day to once a week during a period ranging from 10 weeks to one year. We thought the most optimum and practicable frequency is twice a week for thirteen weeks. Each lesson will last one hour, starting with twenty minutes warming-up and ending with ten minutes cooling down. Hereby Chi Kung exercises will be used. Chi Kung means 'control or mastery of the breath'. Emphasis is placed on relaxation and on contemplation of the breath. In addition to the lessons the participants will be asked to practice the learned Tai Chi Chuan positions at home at least twice a week for about fifteen minutes.

### Outcome measures

The primary outcome measure is new fall accidents. At the end of the baseline measurements participants will receive a fall calendar. They will be asked to fill in daily for a year if they are fallen, nearly fallen or not fallen. A fall is defined as 'an unintentionally coming to rest on the ground, floor, or other lower level'. A near-fall is defined as 'the person seems to fall, but can prevent the fall by catching or leaning on a person or a thing (e.g. a chair, a drawer or a table)' [12].

When a fall or a near-fall is reported people will be asked to give more details (e.g. how it happened, at what time, if they were hurt, if they started to use devices, whether medical care was needed) on an additional standardized form. The forms can be returned in postage free envelopes at the end of each month. If forms are missing or incomplete the research assistant will contact the participant by phone and together they will complete the forms.

### Secondary outcome measures

- Balance is measured with the Berg Balance Scale. It consists of fourteen items that are scored on a five-points ordinal scale [13-15].

- Fear of falling is measured with the Falls Efficacy Scale [16]. It is an oral questionnaire and consists of ten items scored on a four points scale, ranging from 'not concerned at all' to 'very concerned'. Participants are asked about how concerned they are that they might fall while performing a series of ten tasks of progressive difficulty in the home environment.

- Physical parameters: blood pressure and heart rate in rest, FEV1 (i.e. forced expiratory volume during the first second) and PEF (i.e. peak expiratory flow). The latter two are measured by a spirometer.

- Physical activities are measured with the Physical Activity Scale for the Elderly (PASE) [17,18]. It combines the frequency of leisure, household and occupational activities over the previous seven days.

- Functional status is measured with the Groningen Activity Restriction Scale (GARS), covering activities of daily living (ADL) and instrumental activities of daily living (IADL) [19]. It consists of eighteen items scored on a four points scale.

- Quality of life is measured with the EuroQol EQ 5-D. It will be used in the cost-effectiveness analysis [20-22].

- Mental health is measured with the SF-36 (subscales) [23-26].

- Use of walking devices, medication, use of health care services (e.g. GP, specialist, physiotherapy, home care/district nurse), adjustments to the house.

### Follow-up

As shown in table 2 participants will be followed up during twelve months after baseline measurements. At the end of intervention period (i.e. at three month) and twelve months after the baseline measurement all measurements will be performed. At six months only the questionnaire will be send by mail.

**Table 2 T2:** Variables and timing measurements

**Variable**	**Time measured**			
	Baseline	3 months	6 months	12 months

Inclusion and exclusion variables	TQ			
Falls and near-falls	Continuously every day when fall occur			
Severity of fall incidents	Continuously every day when fall occur			
Sociodemografic, physical and environmental factors	WQ			
Balance (Berg Balance Scale)	M	M		M
Fear of falling (Falls Efficacy Scale)	OQ	OQ		OQ
Physical parameters (blood pressure, heart rate, lung function parameters)	M	M		M
Physical activity (Physical Activity Scale for the Elderly)	WQ	WQ	PQ	WQ
Functional status (Groningen Activity Restriction Scale)	WQ	WQ	PQ	WQ
Quality of life (EuroQol)	WQ	WQ	PQ	WQ
Mental health (SF-36)	WQ	WQ	PQ	WQ
Use of walking devices, medication, use of health care services, adjustments to the house	WQ	WQ	PQ	WQ
Compliance to intervention		X		

TQ = telephone questionnaire; WQ = written questionnaire; OQ = oral questionnaire; PQ = written questionnaire send by post; D = diary, by self report, concurrent registration; M = measurement (e.g. by a test); X = reported by teacher

Questionnaires will be checked on missing data and completed with the participants by phone.

In the invitation letter to visit the location for the follow-up measurement at three and twelve months, participants will be asked not to tell the research assistant whether they are allocated to the intervention or the control group. Moreover a reminder sign will be placed on the location. In this way the research assistant will remain masked.

Every effort will be made to keep the loss to follow-up as small as possible. When the questionnaire sent after six months is not received within two weeks, a phone call is made in order to remind the participant.

### Process evaluation

At the end of the intervention period participants and teachers will be asked to fill out a questionnaire to evaluate the Tai Chi Chuan course. This includes the appreciation of the course, the expected benefit, et cetera. The teachers will report their experiences with the protocol, and fill out an attendance list per lesson. Reasons for noncompliance will be written down.

Dropouts will be phoned to get information on the reason of stopping with the course.

These results can be used to optimize the content and implementation of the courses in future. Moreover, it can provide information explaining measured effects or explaining why expected effects were not identified. Moreover a comparison between these self-reported values and the measured values (i.e. Berg Balance Scale) can be made.

### Data entry

Data will be entered in SPSS using a protocol. There will be a check on a random sample of ten percent of the data. Thereafter an overall check will be done using frequency tables to detect unusual values, inconsistencies and missing values.

### Statistical analyses

To assess if randomization was successful, descriptive statistics of baseline characteristics will be used. In case clinically relevant baseline differences regarding prognosis of future incidence of falls is present, effect estimates will be adjusted using multivariate analysis.

Dropouts are defined as participants who stop participating during the first three months (i.e. intervention period). Non-compliers are defined as participants who miss more than twenty percent of the lessons.

The analysis will be performed using the intention-to-treat principle, e.g. all patients are included as randomized irrespective of compliance. Missing values are assigned the last available valid score.

We will evaluate the effect of the intervention in reducing the number of fall incidents using the Student's t-test and survival techniques. To analyze the secondary outcome measures the Student's t-test, the Mann-Whitney test or the Chi-square test will be used according to the type of variable.

When drop out is higher than fifteen percent and/or the compliance is lower than seventy percent an additional per-protocol analysis will be carried out. These are restricted to those participants who complied fully with the intervention protocol and outcome measures.

At the end of the analyses the allocation of participants will be disclosed.

A cost-effectiveness analysis will be conducted alongside the analysis of the clinical data.

Direct costs (such as medication, additional therapy, visits to health care providers) as well as indirect costs (such as disability) measured by the EuroQol, will be related to the primary outcome measure (fall incidents).

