### Randomization

After baseline measurements participants will be assigned to one of the four strata based on gender (male/female) and the prognostic factor fall accidents in the preceding year (yes/no). An independent research assistant will perform randomization into either the control or the intervention group using a randomization list generated by a computer. To avoid unequal group sizes a block randomization will be used using block sizes of four. When two persons live together (e.g. married couples) they will be allocated to the same group, i.e. the group to which the first person contacted is allocated to, in order to avoid contamination.

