## Discussion

As far as we know this is the first trial in Europe considering Tai Chi Chuan and fall prevention. In the United States some similar trials are done, but circumstances differ from Europe since elderly often live in communities. We have to recruit participants via their GP.

Most trials on the effect of Tai Chi Chuan are focused on intermediate outcome measures such as balance, muscular strength, whereas we measure fall incidents.

In this study we use the highest methodological standards. Masking is performed when possible. Moreover randomization will be checked to make clear if baseline characteristics in both groups are equal. If needed adjustments will be made.

The intervention and control group not only differ regarding the intervention, but also in the amount of attention the individuals receive. As social relations integral to the exercise environment are determinants of subjective well-being in older adults [27] we considered to make a third group of elderly, receiving another group-based activity to assess the positive effect of social function of the group. But as this project was restricted in time, the funding organization and we decided to work with two groups. This means that this project will answer a pragmatic research question regarding the efficacy of Tai Chi Chuan regarding fall reduction.

To keep the drop out as low as possible the Tai Chi Chuan-lessons are given at a location close to where the elderly live, the travel costs of the participants will be refunded and as needed we organize transportation.

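### Adjustment is tied to observed baseline imbalance, so the stratification factors, close to balanced by design, would rarely be adjusted for, and which estimate is primary is left open

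*Protocol article*

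**What the plan says.** Under Statistical analyses, the protocol article first checks the allocation: "To assess if randomization was successful, descriptive statistics of baseline characteristics will be used". The adjustment rule follows: "In case clinically relevant baseline differences regarding prognosis of future incidence of falls is present, effect estimates will be adjusted using multivariate analysis". The Discussion repeats it: "Moreover randomization will be checked to make clear if baseline characteristics in both groups are equal. If needed adjustments will be made". No size of difference is given that would count as clinically relevant, and nothing says which estimate leads if both are produced. The number of falls is to be compared with a Student's t-test and survival techniques, with no strata or covariates named.

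Under Randomization, participants are assigned to "one of the four strata based on gender (male/female) and the prognostic factor fall accidents in the preceding year (yes/no", and "a block randomization will be used using block sizes of four". One exception applies: "When two persons live together (e.g. married couples) they will be allocated to the same group". The Background also describes previous falls as strongly related to the risk of falling.

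Under Masking, the researcher who analyses the data is masked. Statistical analyses adds that allocation is disclosed only when the analyses are finished.

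**The concern.** The design and the analysis rule pull in opposite directions. Stratification makes the arms alike on gender and previous fall. A rule that adjusts only for factors on which the arms differ will then pass over those two, including the one singled out as prognostic. If the analysis ignores the strata, its standard error still contains between-stratum variation that the design has already removed from the treatment comparison. Tests are then too cautious and intervals too wide.

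Separately, whether the effect estimate is adjusted turns on a judgement of observed baseline tables against no stated criterion. For the survival analysis this is more than a matter of precision, because an adjusted hazard ratio and an unadjusted one are different quantities.

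This is not a detail awaiting an analysis plan. The article states a rule, and the rule works badly with the stratified design.

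**Working it through.** **Inputs from the protocol article.** Four strata, blocks of four, 135 per group (270 in total), alpha 0.05, beta 0.1 (power 90%), dropout 20%. The 135 per group cannot be reproduced, because no control fall rate, standard deviation or sidedness is given. It is not at issue here; 90% power and a two-sided 5% test serve only as the reference point.

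**Step 1: will the trigger pick up the stratification factors?** An incomplete block of four leaves a difference of at most 2 between arms within a stratum. Previous fallers occupy two strata, so their number can differ by at most 2 × 2 = 4. With about 135 per arm that is 4/135, about 3 percentage points. In a simulation (3000 runs per setting, 216 evaluable participants, which is 270 × 0.8), the larger of the two between-arm differences averaged 1.0 percentage point, with a 95th percentile of about 2. Both results ignore the cohabitant rule.

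**Step 2: how much variance might the strata explain?** The article does not say, so these are assumptions: previous fallers make up p = 40-60% of the sample and fall 2-3 times as often, the overall mean is 1 fall, and the total variance is 2 (negative binomial, k = 1). With m1 and m0 the mean falls of those with and without a previous fall, between-stratum variance is p(1−p)(m1−m0)².

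- p = 0.6, ratio 2: m0 = 1/(0.4 + 1.2) = 0.625, m1 = 1.25; 0.24 × 0.625² = 0.094; R² = 0.094/2 = 4.7%.
- p = 0.5, ratio 2: m0 = 0.667, m1 = 1.333; 0.25 × 0.667² = 0.111; R² = 5.6%.
- p = 0.4, ratio 3: m0 = 0.556, m1 = 1.667; 0.24 × 1.111² = 0.296; R² = 14.8%.

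The range over this grid is 4.7-14.8%.

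**Step 3: what does ignoring the strata cost?** After stratified randomisation the treatment difference has true variance (1−R²)V, while the unadjusted test uses V. It therefore rejects only when the correctly scaled statistic exceeds c = 1.96/√(1−R²).

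- True alpha = 2[1 − Φ(c)].
- Power = Φ(3.24 − c), where 3.24 = 1.96 + 1.28.
- Sample size needed to recover 90% power = [(c + 1.28)/3.24]².
- Reported standard error relative to the true one = 1/√(1−R²).

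| R² | c | True alpha | Power | Sample size factor | SE ratio |
|---|---|---|---|---|---|
| 0.047 | 2.008 | 0.045 | 89.1% | 1.03 | 1.02 |
| 0.05 | 2.011 | 0.044 | 89.1% | 1.03 | 1.03 |
| 0.10 | 2.066 | 0.039 | 88.0% | 1.07 | 1.05 |
| 0.148 | 2.123 | 0.034 | 86.8% | 1.10 | 1.08 |
| 0.20 | 2.191 | 0.028 | 85.3% | 1.15 | 1.12 |

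Over R² of 4.7-14.8% the loss equals about 3-10% of the sample, or 270 × 0.03 ≈ 8 to 270 × 0.10 ≈ 27 participants.

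**Step 4: simulation check.** For assumed previous-fall rate ratios of 1.5 / 2 / 3, type I error was 0.045 / 0.043 / 0.036 unadjusted and 0.047 / 0.048 / 0.043 adjusted for stratum. Power at an assumed treatment rate ratio of 0.5 was 83.7 / 85.5 / 87.7% unadjusted and 83.9 / 86.3 / 88.9% adjusted. The direction is the same and the loss smaller: 0.2, 0.8 and 1.2 points.

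**Step 5: the data-dependent choice.** For another prognostic covariate, adjusting only when the arms differed by an assumed 0.2 SD gave type I error 0.042 / 0.039 / 0.033. Taking the smaller of the adjusted and unadjusted p-values gave 0.059 / 0.051 / 0.045. The Monte Carlo standard error near 5% is √(0.05 × 0.95/3000) ≈ 0.004.

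**The case against.** The strongest reply is that nothing invalid has been planned. That stands: an unadjusted comparison after stratified randomisation errs on the cautious side, and in simulation the imbalance trigger also kept type I error below 5%. A reader might infer that the rule inflates false positives or lets a favourable estimate be picked. The documents do not support that. The trigger looks at baseline characteristics rather than outcomes, the analyst is masked until the end, and choosing the smaller p-value is nowhere proposed. Masking does not, however, supply the missing criterion or say which estimate leads.

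A reader might also use 1/(1−R²) and put the loss at 5-17% of the sample. That overstates lost power, because stratification has already made the estimate itself more precise; the factor describes only the variance reported for it. The power loss is the 3-10% shown above.

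Third, the text does not exclude the stratification factors. Survival techniques could be stratified, and a covariate list may sit in a fuller document. That is fair: their omission is what the stated trigger leads to, not something the article says. The trigger itself is stated twice and can be judged as it stands.

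Finally, the cohabitant rule places the second person without a fresh allocation, and a mixed-sex couple spans two gender strata. Balance may be looser than Step 1 shows, so the trigger could occasionally bring in a stratification factor. The simulation did not model couples, so it is safer to say that the trigger would rarely fire for these factors than that it never would.

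**Conclusion.** The point holds as a modest loss of efficiency together with an open choice of estimate. It is not a threat to validity. The rule tends to leave out the two factors on which the randomisation was built, one of which the article calls prognostic. Under the assumed stratum R² of about 5-15%, true alpha is about 0.044-0.034 instead of 0.05, power is about 89-87% instead of 90%, and reported standard errors are about 2-8% too large. The prevalence, rate ratio, mean and dispersion behind that range are assumptions; the article gives none of them. The formulas are those of a linear comparison of means and do not carry over exactly to a hazard ratio. The direction does not depend on these values, provided the strata predict falls.

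The undefined, data-dependent choice between adjusted and unadjusted estimates is the firmer ground, since it follows from the wording alone. Its effect on error rates looks small in the settings tried.

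**What to change.** Replace the conditional rule under Statistical analyses, and the matching sentence in the Discussion, with a fixed one:

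- The primary falls analysis always includes gender and fall in the preceding year, whatever the baseline tables show. For the number of falls, a count regression takes the place of the t-test. The survival analysis is stratified by these factors or adjusted for them.
- This adjusted estimate is named as primary.
- Baseline tables are descriptive and do not decide the model.
- Any further adjustment prompted by an observed imbalance is labelled a sensitivity analysis.

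No extra data, visits or participants are needed, because both factors are known before randomisation. The cost is small but not nil: the t-test gives way to a standard regression, and an adjusted hazard ratio must be read as conditional on the strata.

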### Sample size and power

The effect of Tai Chi in decreasing fall incidents is conservatively estimated on 25 percent [10]. A power calculation (alpha = 0,05; beta = 0,1; drop out percentage of twenty percent) estimates that 135 participants are needed in each study group. This implies that we intend to enroll 270 participants in total.

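### Last value carried forward is the only missing-data rule and does not exempt the fall diary; applied to falls, it credits people whose diaries stop with fall-free time, and it fills scale scores as if observed

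*Protocol article*

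**What the plan says.** All the analysis rules stand together under Statistical analyses in the protocol article. The analysis is by intention to treat, so that "all patients are included as randomized irrespective of compliance". The next sentence is the missing-data rule: "Missing values are assigned the last available valid score". The primary analysis follows directly and evaluates the intervention in "reducing the number of fall incidents using the Student's t-test and survival techniques". No outcome is exempted, no second rule is given for falls, and no sensitivity analysis for missing data is named. The only analysis linked to dropout is a per-protocol analysis, triggered above 15% dropout or below 70% compliance.

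The primary outcome comes from a daily calendar (Outcome measures): "They will be asked to fill in daily for a year if they are fallen, nearly fallen or not fallen". Dropouts are people who stop within the three-month course. Sample size and power allows for a "drop out percentage of twenty percent".

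Two retrieval measures are described. For fall forms (Outcome measures): "If forms are missing or incomplete the research assistant will contact the participant by phone and together they will complete the forms". For questionnaires (Follow-up): "Questionnaires will be checked on missing data and completed with the participants by phone".

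**The concern.** A fall count grows with the time over which it is recorded. Someone whose diary ends early has fewer recorded falls because fewer days were watched. A t-test on counts that keeps this person needs either the missing time filled or the observed time taken into account. The plan states a fill rule and no exposure adjustment. Carrying a cumulative count forward adds no falls. Carrying the last daily entry forward almost always repeats a day without a fall. Totalling the returned calendars gives the same result.

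The primary comparison then depends partly on who stays. Only one arm is asked to attend a course (twice a week for 13 weeks), so unequal leaving is plausible, in either direction. Costs are to be related to fall incidents, so any distortion also reaches the cost-effectiveness analysis.

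For the scales, what the carried value means depends on when the person left, and the filled value enters the test as though it had been measured.

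**Working it through.** **The plan's own figure.** The 135 per group cannot be recomputed, because no control fall risk, fall rate, standard deviation or sidedness is given. The point does not rest on it. The figures used from the plan are the 20% dropout allowance, the dropout window of months 0 to 3, the 12-month follow-up and the 25% target effect.

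**Assumptions, not in the plan.** A leaver's diary stops on leaving, the fall rate is constant over the year, leavers have the same rate as others, and the dropout splits by arm are as shown.

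**Formula.** With a proportion *d* leaving at time *t* (in years) and the rest of the year counted as no fall, the share of falls still counted in an arm is 1 − *d*(1 − *t*). With no true effect, the ratio of mean counts is the Tai Chi share divided by the control share.

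**Diaries stop at 3 months (*t* = 0.25), the latest point in the dropout definition:**
- 20%/20%: 1 − 0.20 × 0.75 = 0.85 in both arms. Ratio 1.00; any absolute difference shrinks to 85%.
- 25%/15%: 0.8125 / 0.8875 = 0.915.
- 30%/10%: 0.775 / 0.925 = 0.838, an apparent 16% reduction beside a 25% target.
- Reversed, 15%/25%: 0.8875 / 0.8125 = 1.09.

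**Leaving spread evenly over months 0 to 3 (mean 1.5 months, *t* = 0.125):**
- 20%/20%: 1 − 0.20 × 0.875 = 0.825. Ratio 1.00; the absolute difference shrinks to 82.5%.
- 20%/10%: 0.825 / 0.9125 = 0.90.
- 30%/10%: 0.7375 / 0.9125 = 0.81.
- 10%/20%: 0.9125 / 0.825 = 1.11.

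**Effect on the test.** This was simulated with 135 per arm, 1 fall per person-year in controls, Poisson counts and leaving spread over months 0 to 3. The two-sided 5% t-test rejects a true null in about 11% of trials at 20%/10% and about 31% at 30%/10%. With negative-binomial dispersion of 1, these become about 9% and just under 20%. At 20%/20% it stays near 5%, but power for a true ratio of 0.75 falls from about 58% without dropout to below 50% (Poisson). Dividing falls by observed person-time recovers the true ratio in every scenario.

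**Scales, using the timing table under Follow-up:**
- Lost before the 3-month visit: the baseline score becomes the 3- and 12-month score.
- Lost after it: the end-of-course score becomes the 12-month score (or the 6-month value, where a postal questionnaire was returned).
- Precision: if 20% of 135 values are filled, the test counts 135 where 135 × 0.8 = 108 were seen. At an unchanged standard deviation, the standard error is multiplied by √(108/135) = 0.894, about 11% too small.

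**The case against.** The best defence is the word score. The Berg scale, the Falls Efficacy Scale, the GARS and the questionnaires yield scores, whereas a calendar entry does not, so the rule may have been meant for scales only. That reading is open. But falls then have no stated rule, and a t-test on unadjusted counts still credits leavers with fall-free time. What stands is that application to falls is not explicit.

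A reader might infer several stronger things that the document does not support:
- **That the survival analysis is invalid.** Censoring at last contact is a normal part of such methods, and nothing says event times are imputed. That analysis may be unaffected.
- **That one 'fallen' last entry would generate about 270 imputed falls.** This is a rare, literal day-by-day reading. At 1 fall per year, about 1/365 of leavers would be affected, and the expected number filled in (270/365 = 0.74 per leaver) roughly equals the falls missed. It adds extreme variance, and it does not belong with the 0.92 and 0.84 figures, which assume that no falls are added.
- **That Tai Chi is bound to be favoured.** No split by arm is given, equal dropout leaves the ratio at 1.00, and more leaving among controls reverses the bias.
- **That 20% of diaries will be lost.** That figure is a sample-size allowance. Leaving the course need not end the diary, and staff telephone for missing forms. This helps with people still in contact, but cannot supply data for those who withdraw.
- **That early benefit is frozen in dropouts as the plan defines them.** They leave during the course, so any lost before the 3-month visit carry a baseline score. Only people lost later carry an end-of-course score. Nor does the document say that function declines over the year.

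**Conclusion.** The concern holds in a limited form. The article does fix a missing-data rule, so this is not a detail left to an unseen analysis plan, and the rule is unsuitable for both kinds of outcome. For falls, the harm is dilution of the tested difference to about 82.5–85% at 20% dropout in both arms. If dropout is unequal, the ratio is also biased in favour of the arm that loses more people: about 0.92 at 25%/15% and 0.84 at 30%/10% with exit at 3 months, and further from 1 with earlier exit. These sizes depend on the assumed splits, on diaries stopping at exit and on the rule (or plain counting) being used for falls. Successful telephone retrieval would make them smaller. For the scales, the misplacement of scores in time and the overstated precision follow from the rule itself; only their extent depends on how many values are missing. The per-protocol analysis does not repair missing outcomes in the intention-to-treat result.

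**What to change.** Replace the carry-forward sentence with separate rules.

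- **Falls:** do not impute. Analyse falls over observed diary time, for example by negative binomial regression with log person-time as offset, and state that the survival analysis censors at the last diary day.
- **Scales:** use a mixed model for repeated measures on all observed values, or multiple imputation. Keep carry-forward at most as a sensitivity analysis.
- **Sensitivity:** both replacements assume data are missing at random. Add one analysis that departs from this, for example giving Tai Chi leavers control-like values after exit.

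The cost is a change of wording and modest extra programming on data already planned. It would also help to state whether people who leave the course keep their fall calendar to 12 months; if this is not already intended, it is extra data collection and has to be budgeted. The analyst is masked, so the wording can be changed without knowledge of the results, provided this is done before allocation is disclosed.
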